### Trial design {8}

This will be a superiority trial design. This is a pragmatic parallel group (single blind – outcome assessors) randomized controlled trial (NCT04180722) with a nested qualitative evaluation of the 12-month TtLIVE intervention compared to standard of care, with 1:1 allocation of eligible individuals (children and adults) newly transitioning to HMV. The trial was designed in accordance with the established *Standard Protocol Items: Recommendations for Interventional Trials (SPIRIT) guidance* [26]. For participants allocated to the intervention group, the TtLIVE intervention will be delivered through the aTouchAway™ e-platform (via an electronic tablet, Smartphone, or lap/desktop) by a participating specialist HMV program or clinic. For participants allocated to the control group, usual care of their specialist HMV program or clinic will be provided.

## Methods: participants, interventions, and outcomes

### Study setting {9}

This trial will be conducted in 8 HMV programs/clinics in Ontario, Canada. These 8 centers prescribe ≥ 80% of home ventilators to more than 1200 newly transitioning VAIs annually in the province of Ontario, Canada. Adult centers comprise West Park Healthcare Centre, The Ottawa Hospital Rehabilitation Centre, Sunnybrook Health Sciences Centre, and London Health Sciences Centre. Pediatric centers include The Hospital for Sick Children (SickKids), Children’s Hospital of Eastern Ontario (CHEO), McMaster’s Children’s Hospital, and Children’s Hospital, London Health Sciences. The Ontario Ventilator Equipment Pool is funded by the Ministry of Health and Long-term Care in Ontario and provides ventilators on loan to all children and adults in the province of Ontario receiving HMV.

### Eligibility criteria {10}

Inclusion and exclusion criteria for the trial are detailed in Tables 1 and 2.

**Table 1 Tab1:** Inclusion and exclusion criteria for study participants

Inclusion	Exclusion
• Newly initiated (in-hospital or outpatient), defined as within 2 months, on a ventilator for HMV prescribed by a participating clinic	• Projected life expectancy of ≤ 2 months
• Reads, writes, and understands English. If patient does not meet this criterion, they have a caregiver that does	• Significant cognitive impairment and absence/inability of a family caregiver able to use aTouchAway™ or complete questionnaires on the subject’s behalf
• Provides informed consent	• Uncontrolled psychiatric illness
• Live in a non-institutionalized setting	• Enrolled in a research study to evaluate another eHealth platform or care coordination model of care
	• Plan to move outside of province in the next 12 months

**Table 2 Tab2:** Inclusion and exclusion criteria for family caregiver participants

Inclusion	Exclusion
• Primary caregiver of an individual newly initiated on HMV that consents to participation	N/A
• Reads, writes, and understands English	
• Provides informed consent	

### Additional consent provisions for collection and use of participant data and biological specimens {26b}

This trial does not involve collecting biological specimens for storage.

## Interventions

### Explanation for the choice of comparators {6b}

In this trial, control arm participants will receive the current standard of clinical care. Care will be delivered in accordance with the Canadian Thoracic Society (CTS) HMV clinical practice guidelines and include scheduled face-to-face or virtual (due to the COVID-19 pandemic) clinic visits with the HMV team. Additional telephone calls and emails for equipment troubleshooting and management of intercurrent illnesses will depend on medical stability. Other recommended practices include sleep studies and spirometry (where feasible) with frequency based on disease diagnosis and severity; access to the Ontario Ventilator Equipment Pool (VEP) 24-h hotline for ventilator equipment-related issues; an action plan for acute respiratory infection and/or deterioration/disease progression; and a troubleshooting plan for ventilator-related issues. In addition, all patients are offered remote ventilator monitoring.

Proactive bi-monthly monitoring of symptoms is not standard of care at the eight participating study sites where care outside of scheduled clinic visits is reactive and in response to VAI and family caregiver-raised causes for concern. VAIs or family caregivers can contact a member of the HMV team at each of the eight study sites outside of scheduled clinic visits during business hours for assistance with such issues. After business hours clinical issues and emergencies are directed to the ED.

### Intervention description {11a}

Each intervention group participant will receive the TtLIVE intervention delivered through the aTouchAway™ e-platform (Aetonix, Ottawa, Canada). TtLIVE comprises five main components: scheduled virtual clinic visits, virtual care and action plans, bimonthly and monthly monitoring of symptoms, monitoring of ventilator usage and related issues, and as needed virtual consultation and education resources (Table 3).

**Table 3 Tab3:** TtLIVE components

Intervention feature	Details
**Scheduled virtual clinic visits**	I. Virtual clinic visits with VAI, family, and HMV clinical team over the aTouchAway™ platform will be scheduled at the usual frequency of face-to-face or virtual clinic visits in the standard of care group. II. Structure and content will be based on the structure and content of usual care face-to-face or virtual ventilator clinic visit and include clinical history and symptoms, ventilator data download reports, airway clearance device data downloads, and ventilator alarm review and plan of care.
**Virtual care plan and action plan**	I. Co-developed by and accessible to VAI, family, and nominated circle of care members II. Summary of medical diagnoses, medications, allergies, ventilator and cough assist settings and alarms, and special precautions III. Bespoke action plan for clinical and equipment-related issues developed by each clinical team as part of standard clinical care
**Scheduled monitoring**	I. Bimonthly monitoring with the VentSS questionnaire of symptoms/signs, ventilator usage, and/or ventilator-related equipment issues and/or alarms indicative of respiratory infection and/or deterioration/ disease progression II. Programmed daily and/or weekly reminders to encourage adherence with equipment use and/or maintenance III. Monthly monitoring with the S^3^-NIV questionnaire of symptoms/signs, ventilator usage, and/or ventilator-related equipment issues IV. Remote monitoring of ventilators
**Scheduled as needed Consultation** over the aTouchAway™ platform	I. Triggered by concerning symptoms and/or ventilator parameters (ie yellow or red monitoring alerts) II. Requested by VAI/family and/or healthcare providers III. Secure messaging, voice call, virtual or face-to-face visit
**Education resource library**	I. Access to documents and videos customized to their technology type. For example, ventilator cleaning guides, education refreshers on equipment, and methods for troubleshooting ventilator problems.

#### Intervention delivery

*Scheduled virtual clinic visits* will take place during the first week of trial enrolment and then at 3 months (±2 weeks), 6 months (±2 weeks), 9 months (±2 weeks), and 12 months (±2 weeks) depending on medical stability. Visit frequency aligns with usual care in-person or virtual visits.

A virtual care plan will be completed in partnership with the participant, caregiver, and health care team. This will include a summary of medical diagnoses, medications, allergies, ventilator and cough assist settings, and alarms as well as special precautions. The healthcare providers that are within the circle of care for the participant, will be given permission to access their “virtual chart.” In addition, during the first visit, a *virtual action plan* will be developed by the HMV team in partnership with the participant and caregiver to address clinical and/or ventilator-related concerns. This care plan will include triggers for plan activation and actions in the event of respiratory infection/deterioration and ventilator alarm issues. A pre-determined calling tree is embedded to enable timely and appropriate response from the appropriate responder for medical and ventilator concerns.

*Routine monitoring* of clinical symptoms, ventilator usage, and other equipment-related issues will be conducted through participant bimonthly (VentSS) and monthly (S^3^-NIV) questionnaires administered and answered over the aTouchAway™ platform. We have selected the S^3^-NIV questionnaire, developed for telemonitoring of patients using NIV [25], as our monthly questionnaire. We have included an adapted version for the study participants using invasive ventilation.

*As needed scheduled clinical consultations* can be requested by the VAI, caregiver, and/or healthcare providers in the event of (1) abnormal parameters detected from routine data monitoring (i.e., questionnaire responses yield yellow or red notifications to the healthcare team); and (2) requests made by the VAI or caregiver. We have programmed questionnaire responses within the aTouchaway platform so that one response of concern results in a yellow notification and > 1 results in a red notification.

#### Intervention training

VAIs and their family members will be able to access aTouchAway™ on a range of devices including laptops, desktops, tablets, and Smartphones. Participants without access to a reliable smart device and internet will be offered a study tablet. Prior to distributing the tablet, the research team will create a secure, encrypted account for that VAI. VAIs and the families will receive formalized training (onboarding) on the TtLIVE intervention (via home or virtual visit) by a member of the research team. Instruction will be given on how to (1) operate and navigate the aTouchAway™ platform; (2) complete the virtual care plan; (3) initiate a telephone/ videoconference call; and (4) how to document and upload the ventilator and symptom monitoring data to the ventilator team.

Healthcare providers will use computers and/or smartphones enabled with aTouchAway™ to access the TtLIVE intervention. A research team member will train healthcare providers on the process of downloading the platform onto their device, creating their account, and adding them to the circle of care for a VAI.

### Criteria for discontinuing or modifying allocated interventions {11b}

The TtLIVE intervention would be discontinued if requested by a participant.

### Strategies to improve adherence to the intervention {11c}

A multimodal strategy will be employed to enhance TtLIVE intervention adherence. Study participants that do not complete their symptom and ventilator surveys within an a priori established period of 24 h or 48 h will receive two reminders via the aTouchAway™ app for each questionnaire needing completion. Intervention participants will also have access to the unblinded research coordinator through secure messaging, phone, or video call to troubleshoot any issues, review the app features, or answer any questions.

### Relevant concomitant care permitted or prohibited during the trial {11d}

Co-enrolment in another research study involving an eHealth intervention or care coordination model of care will be prohibited for the duration of the study period.

### Provisions for post-trial care {30}

Towards the end of the 12-month study period, the local HMV team will prepare the patients, caregivers, and healthcare providers for transition back to usual care for study participants allocated to the intervention group.

### Outcomes {12}

See Table 4 for a list of study outcomes.

**Table 4 Tab4:** Study outcomes and study measures/instruments

Study outcomes	Measure/instrument
Co-primary outcomes	
ED visit rates at 12 months	Health administrative data and AHCR-hybrid
Change in family caregiver reported sense of mastery at 12 months	Pearlin Self-Mastery Scale score
Secondary outcomes	
Healthcare utilization outcomes	
Number of hospital admissions and days in hospital over 6 and 12 months	Health administrative data and AHCR-hybrid
Hospital free survival at 6 and 12 months	Health administrative data and AHCR-hybrid
Time to first ED visit and first hospital admission	Health administrative data and AHCR-hybrid
Overall survival at 6 and 12 months	Health administrative data and AHCR-hybrid
Number and type of outpatient specialist visits at 6 and 12 months	Health administrative data and AHCR-hybrid
Number of family physician visits at 6 and 12 months	Health administrative data and AHCR-hybrid
Homecare service use at 6 and 12 months	Health administrative data and AHCR-hybrid
Participant and caregiver outcomes	
Change in caregiver burden from baseline to 6 and 12 months	Zarit Burden Interview
Change in VAI health-related quality of life (HrQoL) from baseline to 6 and 12 months	EQ-5D-5L (adults) and EQ-5DY (children)
Change in patient reported sense of mastery at 12 months	Pearlin Self-Mastery Scale score
Ventilator use/alarms and signs and symptoms questionnaire	VentSS and the S^3^-NIV questionnaires
Economic outcomes	
Cost utility (ICER) of TtLIVE intervention compared to usual care in improving patient utility	AHCR-hybrid; provincial datasets (IC/ES); provincial costing sources (OCCI); EQ-5D-5L (adults) and EQ-5DY (children)
Healthcare provider outcomes	
Healthcare provider time	Care Coordination Measurement Tool
Process measure outcomes	
Quality of care coordination	Family Experiences of Care Coordination
Adherence to TtLIVE intervention by VAIs/family caregivers over 12 months and platform usage	aTouchAway Metrics
Adherence to TtLIVE intervention by healthcare providers over 12 months and platform usage	aTouchAway Metrics
Adverse events	
Adverse events unique to the use of the aTouchAway™ platform and the internet (technical issues due to software (aTouchAway™ platform) or hardware (the iPad/ phone/ computer being used) failure, privacy, and security breach	Direct reporting from Aetonix, patient, and caregiver

### Data collection

#### Baseline data

We will collect baseline demographic, medical, and psychosocial data on study enrolment. An unblinded Research Coordinator will contact participants via telephone to collect this and notify participants of study allocation following consent and randomization.

##### VAI demographics and characteristics

We will document demographic, medical, and psychosocial characteristics that include smoking status/history and number of pack years (teens and adults); influenza, pneumovax vaccination and COVID-19 status; other medical technology at home; number of hours and type of homecare provider support; and distance (km) from referral ventilation center. We will collect participant’s health card number (Ontario Health Insurance Plan (OHIP) number), date of birth, sex, and randomization allocation for linking to health care databases that contain information about physician, hospital, home care services, and medications that are paid for through universal health insurance administered by the Ontario government.

##### Caregiver demographics and characteristics

The following demographic characteristics will be obtained from the primary caregiver: age, sex, marital status, family income, the highest level of education, and employment status.

#### Healthcare utilization and costs

##### Health administrative data

We will use provincial health administrative data (facilitated through Institute of Clinical Evaluative Science [IC/ES]), collected by the province of Ontario for the administration of its universal health care system, to obtain data on health utilization outcomes over the 12-month trial period. We will verify other public healthcare utilization through participant self-report using the AHCR-hybrid.

Seven provincial health administrative databases will be used: the Ontario Health Insurance Plan Physicians Services Database for information about physician visits; the Canadian Institute of Health Information (CIHI) Discharge Abstract Database for information on hospital admissions; the CIHI National Ambulatory Care Reporting System for information about emergency department visits and ambulatory day surgeries, the Registered Persons Database for demographic information and deaths outside of a hospital setting; the Ontario Home Care Database for information about provincially funded home care use; and the National Rehabilitation Reporting System for information on in-participant rehabilitation programs.

Participant/caregiver study information will be linked deterministically to the health administrative data using healthcare numbers provided to all individuals insured by the Ontario Health Insurance plan. This will be encrypted for privacy and security. Analysis of linked data will occur within the safe and secure computing environment, and according to the privacy policies of ICES (ICES.on.ca). Study investigators will be provided de-identified summary data.

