**Objectives and brief methods:**

Our primary objective is to evaluate the TtLIVE intervention compared to a usual care control group using an eight-center, pragmatic, parallel-group single-blind (outcome assessors) randomized controlled trial. Eligible patients are children and adults newly transitioning to HMV in Ontario, Canada. Our target sample size is 440 participants (220 each arm). Our co-primary outcomes are a number of emergency department (ED) visits in the 12 months after randomization and change in family caregiver (FC) reported Pearlin Mastery Scale score from baseline to 12 months. Secondary outcomes also measured in the 12 months post randomization include healthcare utilization measured using a hybrid Ambulatory Home Care Record (AHCR-hybrid), FC burden using the Zarit Burden Interview, and health-related quality of life using the EQ-5D. In addition, we will conduct a cost-utility analysis over a 1-year time horizon and measure process outcomes including healthcare provider time using the Care Coordination Measurement Tool. We will use qualitative interviews in a subset of study participants to understand acceptability, barriers, and facilitators to the TtLIVE intervention. We will administer the Family Experiences with Care Coordination (FECC) to interview participants. We will use Poisson regression for a number of ED visits at 12 months. We will use linear regression for the Pearlin Mastery scale score at 12 months. We will adjust for the baseline score to estimate the effect of the intervention on the primary outcomes. Analysis of secondary outcomes will employ regression, causal, and linear mixed modeling. Primary analysis will follow intention-to-treat principles. We have Research Ethics Board approval from SickKids, Children’s Hospital Eastern Ontario, McMaster Children’s Hospital, Children’s Hospital-London Health Sciences, Sunnybrook Hospital, London Health Sciences, West Park Healthcare Centre, and Ottawa Hospital.

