##### Ambulatory Home Care Record-Hybrid (AHCR-hybrid)

In addition to the AHCR [27], a hybrid form was developed with a set of customized study-specific questions [28] which was appended to better capture the data needs of the planned economic evaluation. We will use the AHCR-hybrid to collect health care resource utilization. Completed monthly, it will be used to capture public and private healthcare utilization including ED visits, hospitalizations, ambulatory/out-patient, and home-based health services. The tool will also capture patient and caregiver private and out-of-pocket health care expenditures, lost productivity relating to caregiving or obtaining medical care as well as adverse events or performance issues related to the use of aTouchAway™ platform and the internet.

Intervention costs for the technology, the aTouchAway^TM^ platform, will be obtained from commercial pricing as well as study data. Both implementation and annual maintenance costs for the intervention will be determined on a per-patient basis and assigned to each participant in the intervention arm.

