**Participants (with/without caregiver assistance)**								
Demographic/baseline data	10–15 min	X						
Ambulatory and Home Care Record (Hybrid) [27,28 ]	10–20 min	X	X					
Euro-Quality of Life- 5D-5L Dimensions Scale [32,33] (5D-Y for kids)	10–15 min	X					X	X
Qualitative interviews**	60 min						X	X
S3-NIV*** [6]	5 min	X		X				
Pearlin Self-Mastery Scale	5 min	X				X	X	X
VentSS***			X					

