## Statistical methods

### Statistical methods for primary and secondary outcomes {20a}

The number of ED visits will be analyzed using Poisson or negative binomial regression. Pearlin Mastery Scale scores at 12 months will be analyzed using linear or robust regression models depending on the distribution of the data and adjusting for baseline Pearlin score. Both analyses will adjust for the for the stratified clinical site. We will conduct a secondary analysis of the primary outcome, ED visits, adjusting for a priori chosen clinically important covariates: age, sex, and clinical site; and stratified by pediatric, adult ALS, and adult non-ALS and ventilation type (invasive or non-invasive ventilation). Analysis of secondary outcomes, viewed as exploratory in nature, will vary depending on the outcome: count data (i.e., number of hospitalizations) will be compared with Poisson or negative binomial regression as appropriate; hospital free survival via Kaplan- Meier curves and Cox proportional hazards; time to ED admission and hospitalization using Fine and Gray models to account for competing risk of death; continuous repeated measures outcomes (EQ-5D-3L/5D-Y, FECC, ZBI, and CCMT) using linear mixed effects models.

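### Neither ED-visit model uses ED visits before randomisation, although the planned record linkage could supply that count; the cost is precision, not bias

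*Protocol article*

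**What the plan says.** **Models.** Statistical methods {20a} gives Poisson or negative binomial regression for the number of ED visits, adjusted for clinical site. A secondary ED analysis is described as "adjusting for a priori chosen clinically important covariates: age, sex, and clinical site", and it is stratified by paediatric, adult ALS and adult non-ALS group and by ventilation type. The section specifies baseline adjustment for the Pearlin score only.

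**Linkage.** The Health administrative data section says provincial records are used "to obtain data on health utilization outcomes over the 12-month trial period". The ED source is "the CIHI National Ambulatory Care Reporting System for information about emergency department visits and ambulatory day surgeries". The VAI demographics section lists the health card number and "randomization allocation for linking to health care databases that contain information about physician, hospital, home care services", with no date limit.

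**Self-report.** Table 5 schedules the "Ambulatory and Home Care Record (Hybrid)" at baseline and every 4 weeks. The AHCR-hybrid section says "it will be used to capture public and private healthcare utilization including ED visits", but gives no recall period. No ED model uses the baseline form.

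**Abstract.** It says: "We will adjust for the baseline score to estimate the effect of the intervention on the primary outcomes".

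**The concern.** The sample-size section itself treats ED visits as overdispersed: it simulates from a negative binomial with half of patients having no visit. If part of that spread reflects patients who attend often year after year, a prior-year count would explain some of it. Left out, that variation stays in the error of a co-primary comparison, and a chance imbalance in frequent attenders goes unadjusted. A count dated before randomisation cannot be affected by allocation. The covariates are written into {20a}, so leaving out prior ED visits is a choice the article makes, and it can be reviewed as one.

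**Working it through.** **Inputs from Sample size {14}:** control rate 1.3 visits per year, 50% with no visit, rate ratio 0.70 (0.91/1.3), alpha 5% (taken as two-sided), power 80%, 200 per group. **Not given:** the dispersion k, and the correlation between prior-year and trial-year ED visits.

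**Step 1. The plan's own figure.** For a Wald test of the log rate ratio under a negative binomial:

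- V = (1/1.3 + k) + (1/0.91 + k) = 1.868 + 2k
- n per arm = (1.960 + 0.842)² × V / (ln 0.70)² = 7.849 × V / 0.1272
- power at n per arm = Φ(0.3567 / √(V/n) − 1.960)

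Reading the inputs as one negative binomial, (1 + 1.3k)^(−1/k) = 0.5 gives k = 1.66. Then V = 5.18, n = 320 per arm, and at 200 per arm the standard error is √(5.18/200) = 0.161 and power is 60%. The stated 200 per arm needs k of about 0.69, which implies 39% with no visit. The article does not print its dispersion, so both values are carried forward. Whether 200 per arm is right is a separate question.

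**Step 2. Gain if the covariate removes a share of the overdispersion.** Replace k by k × (1 − share):

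| Share removed | k = 1.66: n per arm | k = 1.66: power at 200 | k = 0.69: n per arm | k = 0.69: power at 200 |
|---|---|---|---|---|
| 0% | 320 | 60% | 200 | 80% |
| 20% | 279 | 66% | 184 | 83% |
| 40% | 238 | 73% | 167 | 87% |
| 60% | 198 | 81% | 150 | 90% |

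**Step 3. Simulation over assumed correlations.** Correlated gamma frailties were drawn for the prior and trial years, with k = 1.66, 200 per arm and rate ratio 0.70. Negative binomial models were fitted with and without the log prior-year count. Set A used 600 trials per setting and log(count + 0.5), with a Monte Carlo error of about 2 points. Set B used 1,500 trials and log(1 + count), with an error of about 1.3 points.

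| Set | Count correlation | Power without | Power with | Gain (points) |
|---|---|---|---|---|
| A | 0.16 | 59.3% | 60.7% | 1.3 |
| A | 0.28 | 56.8% | 61.8% | 5.0 |
| A | 0.41 | 62.3% | 69.0% | 6.7 |
| A | 0.57 | 59.8% | 75.5% | 15.7 |
| B | 0.29 | 59.0% | 63.3% | 4.3 |
| B | 0.43 | 59.8% | 67.9% | 8.1 |
| B | 0.59 | 62.4% | 75.1% | 12.7 |

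The gain at 0.16 is within simulation error. A further run gave median model standard errors of 0.161 without and 0.158 with the covariate at that correlation. By the Step 1 formula, that moves power from 60.1% to 61.7%, or about 2 points.

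**Step 4. Type I error.** Set A had one null run, at a count correlation of about 0.44: the adjusted model rejected 7.5% and the unadjusted 5.2% (error about 0.9 point). The three larger null runs in set B gave 6.1% against 5.8%, 4.1% against 4.3%, and 5.9% against 4.9% (error about 0.6 point). They show no clear inflation.

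**The case against.** **The linkage is not limited to the trial year.** A reader might infer from "to obtain data on health utilization outcomes over the 12-month trial period" that earlier records will not be drawn and the prior count is lost. The sentence concerns outcomes, which follow randomisation by definition, and the linkage is described elsewhere without dates. Records can still be drawn retrospectively. This objection stands; what remains is that no look-back is stated.

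**A baseline measure exists.** A reader might conclude that no ED measure is planned at baseline. The baseline AHCR-hybrid contradicts that. It is self-reported with an unstated recall period, and no ED model uses it.

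**The abstract is only loosely worded.** Its plural might be read as promising baseline adjustment for ED visits. The sentence follows the one on the Pearlin scale, and {20a} ties baseline adjustment to that scale. It does not support a claim of conflicting ED models.

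**Extraction windows belong elsewhere.** Section {31c} mentions a dataset creation plan, which may set a look-back. That answers the extraction half of the point. It does not answer the model half, because {20a} names the covariates.

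**The benefit is unproven and may be small.** No figure shows that prior visits are the best predictor. Participants are within 2 months of starting ventilation, so the look-back year is mostly before it and carry-over may be weak. Site, diagnosis group and ventilation type already capture some between-patient variation, and the simulations omit them. In set B at correlation 0.29, the empirical variance of the log rate ratio fell only 2% to 3%, less than the 8% suggested by model standard errors. All of this stands and limits the size claimed.

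**Validity is intact.** Allocation is randomised and stratified, so omitting a prognostic covariate does not bias the comparison. This also stands.

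**Conclusion.** The point holds as one about precision: the ED models in {20a} leave out a pre-randomisation ED count that the planned linkage could supply cheaply. The documents do not support calling it bias, lost data or a contradiction.

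At k = 1.66, the gain at 200 per arm runs from about 2 points, hardly distinguishable from none, to about 16 points over count correlations of about 0.16 to 0.6. At k = 0.69, power would rise from 80% to about 83% to 90% if the covariate removed 20% to 60% of the overdispersion. Both ranges rest on an assumed correlation or share removed and on a dispersion the article does not print. They are measured against a model without site or strata terms, so the increment over the planned model may be smaller.

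**What to change.** In Statistical methods {20a}, prespecify log(1 + ED visits in the 12 months before randomisation) as a covariate in the co-primary ED model, alongside site. Fix this before outcome data are seen.

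In the Health administrative data section, state that the linked extraction covers those 12 months for both arms. For infants under 1 year, use the visit rate over available life with an indicator for a short look-back.

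The cost is one line in the extraction specification and one covariate in the model, with no new visit or patient contact. The downsides are a longer extraction window and a less informative look-back in infants.
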